### Primary analysis

Initially, scatterplots of outcome variables and exercise dose variables will be used to suggest starting model structures and possible more complex alternatives. The structures of the models used for the dose-response analysis will depend on the specific relationship between change in gait speed and the exercise dose variable. Because of this, and not having any prior knowledge of the structure of the relationship, multiple models will be fitted and evaluated by R-squared values to identify the models that fit data the best. As a starting point, the first model will be fitted as a fixed increase in outcome, based on exercise dose-change done by linear regression modelling. If necessary, more complex regression such as polynomial relationship and other nonlinear structures will also be evaluated.

In the case that none of the models seem to fit the data, a linear regression model with a categorical variable based on intervals of the exercise dose variable will be fitted. This model does not provide a direct dose response relationship but provides an estimate of the association between the outcome variable and the exercise dose variable within the specific intervals.

“Regression to the mean” may be present and will be evaluated by the correlation between the change and the measure at baseline. If regression to the mean is believed to be present for an outcome, the models of the outcome will additional include the baseline measure to adjust for regression to the mean.

Possible confounding variables (self-efficacy (baseline), physical activity (during intervention), and gait speed (baseline)) will also be included in the models. The confounding effect of each variable will be examined by comparison of dose response estimates in models with and without the confounder. If there is no relevant change between the estimates of the models, the confounder will be excluded from the model. Normality assumptions in the models are evaluated by QQ-plots

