### Outcomes

***Exposure.*** Performed exercise dose will be quantified as the total physiological exercise stimulus (Time under tension summary dose per week) recorded by a sensor (Bandcizer: commercially available from
www.bandcizer.com) attached to the elastic exercise band. The sensor automatically switches on and stores data when the elastic exercise band is used
^13,
14^. Furthermore, performed exercise dose will be quantified as the number of days with strengthening exercises being performed.

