### Sample size

The sample size estimation is based on a minimal clinical important difference of 0.2 m/sec
^34^ between changes in gait speed among participants with highest performed exercise dose compared to participants with smallest performed exercise dose. Based on results from a pilot study leading up to this trial, we expect a maximal difference of 4 hours in performed exercise dose (total Time under tension summary dose) during the 7-week intervention period between participants with highest and lowest exercise compliance. Also based on the pilot study, a SD of 1.06 hours for exercise dose and 0.16 m/sec for change in gait speed were used. The power is set at 0.90 to increase the power for secondary analyses, and with a 0.05 level of significance. Based on the above, the required sample size is estimated to be 88 participants.

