### Statistical methods

All the planned analyses are listed in
Table 3.

**Table 3. T3:** Variables, measures and methods of analysis.

Variable/outcome	Hypothesis	Outcome measure (unit, scale)	Methods of analysis
Demographic variables	Descriptive statistics, no hypothesis	Age, gender, height, weight, ASA status	Summary statistics
Supplementary descriptive variables	Descriptive statistics, no hypothesis	Prosthesis type, prior total joint replacement, length of hospital stay and self-efficacy (prior to surgery and baseline)	Summary statistics
Performed exercise dose of elastic band resistance training (exposure)	Descriptive statistics, no hypothesis	Time under tension summary dose/week and total (continuous) Number of exercise sessions/ week and total (number, continuous)	Summary statistics
1. Primary analysis			
Gait speed – measured by 40-m fast-paced walk test	Dose-response relationship	Change in score from baseline to follow up (meters/second, continuous)	(Described in more detail in section 2.12.1) Scatterplots of outcome variables and exercise dose variables will be used to suggest starting model structures and possible more complex alternatives. The analysis will depend on the specific relationship between change in gait speed and the exercise dose variable. Multiple models will be fitted and evaluated by R-squared values to identify the models that fit data the best. 1) The first model will be fitted as a fixed increase in outcome, based on exercise dose-change done by linear regression modelling. 2) If necessary, more complex regression, such as polynomial relationship and other nonlinear structures, will also be evaluated. 3) In the case that none of the models seem to fit the data, a linear regression model with a categorical variable based on intervals of the exercise dose variable will be fitted. If the measure at baseline correlates with the change, baseline measure will be adjusted for. The effect of possible confounding variables will be examined and, if having an effect, the confounder(s) will be adjusted for.
2. Secondary analyses			
HOOS ADL	Dose-response relationship	Change in score from baseline to follow up (points, continuous)	Similar to the primary analysis

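### The primary dose-response model is chosen from the data by unpenalised R-squared, while the 88 participants are sized for one linear slope, so the stated 0.05 level and 0.90 power are not both guaranteed

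*Protocol article*

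**What the plan says.** The Primary analysis section starts from scatterplots of outcome against dose, which are to suggest model structures. Because the shape of the relationship is unknown, "multiple models will be fitted and evaluated by R-squared values to identify the models that fit data the best". Table 3 under Statistical methods repeats this: "Multiple models will be fitted and evaluated by R-squared values to identify the models that fit data the best". Both places give the same order: a linear model first, then polynomial or other non-linear forms where needed, then a model with dose categories if nothing appears to fit. Neither place closes the list of candidates, says when complexity is needed, defines adequate fit or gives category cut-points. R-squared is the only criterion named. The Secondary analyses section applies the same approach to HOOS ADL.

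The Sample size section sets definite error rates: "The power is set at 0.90 to increase the power for secondary analyses, and with a 0.05 level of significance". Its inputs are a difference of 0.2 m/s in gait-speed change, a dose range of 4 hours, and SDs of 1.06 hours and 0.16 m/s.

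**The concern.** The selection rule has no penalty for complexity. Among nested polynomials the larger model always has an R-squared at least as high, so the rule gives no information on whether the extra terms are real. The structure is also suggested by the same 88 outcomes on which it would then be tested.

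The sample size, however, is that of a single 1-df test. If a 3-df curve replaces the line, power is lost when the truth is linear. If a second model gets a chance after the first fails, type I error rises. This is the study's only powered analysis, and the Discussion says that the results will be used to plan and power a randomised trial, so an overfitted curve could carry into that design.

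**Working it through.** **Inputs** (all from the Sample size section): effect "The sample size estimation is based on a minimal clinical important difference of 0.2 m/sec"; dose range, "we expect a maximal difference of 4 hours in performed exercise dose"; SD of dose 1.06 h; SD of change 0.16 m/s; power 0.90; "with a 0.05 level of significance". Sidedness is not stated, and two-sided is assumed.

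**Reproducing the 88**
- Slope: 0.2 / 4 = 0.05 m/s per hour.
- Correlation: r = 0.05 × 1.06 / 0.16 = 0.331, so R-squared = 0.110.
- Residual SD: √(0.16² − 0.053²) = 0.151 m/s.
- Noncentrality at n = 88: 0.053 × √88 / 0.151 ≈ 3.29. The noncentral t with 86 df gives power 0.903. At n = 87 power is 0.899, so 88 is the smallest n that reaches 0.90.

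Other readings do not give 88: one-sided 71, normal approximation 86, Fisher z 92, and 98 if 0.16 is taken as the residual SD. The stated size is that of one linear slope on total time under tension.

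**Same effect, more degrees of freedom.** With R-squared 0.110 and n = 88, the overall F test has power 0.903 with 1 df, 0.834 with 2 df and 0.777 with 3 df.

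**Selection, by simulation.** n = 88, normal dose and errors, 8,000 to 20,000 data sets per scenario, overall test at nominal 0.05, no confounder selection. The candidate sets are assumptions, because the article lists none. Planned effect means a true linear slope of 0.05 m/s per hour.

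| How the model is reached | Type I error | Power at planned effect |
|---|---|---|
| Linear slope fixed in advance | 0.049 | 0.89 |
| Highest R-squared: linear, quadratic, cubic (always the cubic) | 0.05 | 0.76 |
| Highest R-squared: the above plus log, square root, exponential | 0.06 | 0.78 |
| Highest R-squared: linear, quadratic, cubic, one searched breakpoint | 0.088 | 0.83 |
| Highest R-squared among 1-df forms: linear, log, square root | 0.067 | 0.90 |
| Cubic, then quartile categories if not significant | 0.09 | 0.80 to 0.81 |
| Linear kept unless the added quadratic and cubic terms are jointly significant | 0.08 | 0.89 |

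With quadratic and cubic terms available, highest R-squared never returned the linear model in 20,000 data sets, with or without an effect. No selection route examined gave both 0.05 and 0.90.

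**The case against.** Four points on the other side have weight.

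1. **The procedure is stepwise.** Linear comes first and complexity is added only where needed, so the line may be kept. This stands, and it is why the last row of the table shows almost no loss of power. But the trigger is undefined, and the one criterion named always favours leaving the line.
2. **Categories are a fallback.** A reader might let dose quartiles compete with the cubic on R-squared and conclude that the rule itself clearly inflates type I error, so that neither stated figure holds. The text does not set up that contest: the categorical model enters only after the others are judged not to fit. Among common continuous forms alone, the 5% level roughly holds and power is what suffers.
3. **The dose measure is largely fixed.** A reader might infer a second layer of selection, since the Outcomes section adds that "Furthermore, performed exercise dose will be quantified as the number of days with strengthening exercises being performed". The section on handling of missing data, however, ranks the sensor measures: total time under tension, then repetitions, then days, each used only if the one before is not available. Diary days are a sensitivity analysis. The sample size also uses total time under tension, and nothing tells the analyst to choose the measure by fit. No inflation should be claimed on this ground.
4. **The aim is preliminary.** The objective is to indicate preliminary efficacy, the article gives a reason for flexibility, and the Primary analysis section names no p-value or overall F test. This softens the consequence. It does not remove the mismatch, because the article attaches a 0.05 level and 0.90 power to this comparison.

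**Conclusion.** The concern holds in a limited form. The rule selects the primary model from the observed outcomes with a criterion that cannot judge complexity, while the 88 is correct arithmetic for a different, fixed analysis. The two stated error rates are not both guaranteed. Across the assumed routes, type I error runs from about 0.05 to 0.09 and power from about 0.76 to 0.90, and which of the two fails depends on choices the article leaves open. That both must fail is not supported.

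The figures assume a two-sided test, 0.16 m/s as the total SD of change, a normally distributed dose, inference by the overall test of the chosen model, and a truly linear effect of the planned size. The data-driven exclusion of confounders and the conditional baseline adjustment in the Primary analysis section add further selection that was not simulated.

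**What to change.** In the Primary analysis section and Table 3:

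- Name the primary test: the linear slope of change in gait speed on total sensor time under tension over the 7 weeks, two-sided 5%, adjusted for baseline gait speed.
- Pre-specify the adjusted model for self-efficacy and physical activity, instead of keeping or dropping them by comparing estimates.
- Report the slope per hour and as the 4-hour contrast with its 95% confidence interval, set against 0.2 m/s.
- Delete selection by R-squared. Pre-specify one non-linearity check (a quadratic term or a 3-knot spline, judged by F test or AIC). Label this check and the categorical model exploratory and unable to replace the primary result.
- Keep the existing ranking of dose measures. Carry the same wording over to HOOS ADL.

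The cost is rewording before unblinding, with no change in N. A single fixed linear slope gives type I error 0.05 and power 0.90 at n = 88 for the unadjusted test. Covariate adjustment can move power either way, and the article gives no correlations from which to say by how much. The downside is that a strongly non-monotone relationship would appear only in the exploratory check.

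### The last-resort step of the primary analysis cuts the continuous exercise dose into intervals, giving up the slope the study was sized on and, if the relation is in fact linear, power as well

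*Protocol article*

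**What the plan says.** The Sample size section plans for a slope. It takes a "minimal clinical important difference of 0.2 m/sec" between participants with the highest and the lowest dose, and for the dose range "we expect a maximal difference of 4 hours in performed exercise dose". It adds that "a SD of 1.06 hours for exercise dose and 0.16 m/sec for change in gait speed were used". Power is 0.90 "with a 0.05 level of significance", and "the required sample size is estimated to be 88 participants".

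The Primary analysis section and Table 3 set out three steps. Linear regression on dose comes first. Polynomial or other nonlinear forms follow if needed, with models judged by R-squared. If none of these appears to fit, "a linear regression model with a categorical variable based on intervals of the exercise dose variable will be fitted". The section then states the limitation openly: "This model does not provide a direct dose response relationship but provides an estimate of the association between the outcome variable". Under Secondary analyses, HOOS ADL is to be analysed in the same way.

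**The concern.** Sensor time under tension is a continuous exposure, and the 88 participants were justified by a test of its slope. Cutting it into intervals discards the dose differences within each interval and, in an overall test, spends one degree of freedom for each interval beyond the first. The result is a set of interval means, not an increase in gait speed per hour of exercise that can be compared with 0.2 m/s over 4 hours.

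The condition for getting there is that no model seems to fit, with no criterion attached. The only fit measure named is R-squared. With the effect size the protocol plans for, R-squared is small even when the straight line is exactly right. The fallback could therefore be entered because the effect is modest, not because the relation has an unusual shape.

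**Working it through.** **Inputs, all from Sample size:** difference 0.2 m/s; dose range 4 h; SD of dose 1.06 h; SD of change in gait speed 0.16 m/s; power 0.90; alpha 0.05 (taken as two-sided); n = 88.

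**Step 1: reproduce the plan's figure.**
- Slope = 0.2 / 4 = 0.05 m/s per hour.
- Correlation r = 0.05 × 1.06 / 0.16 = 0.331, so R² = 0.1097.
- Residual SD = 0.16 × √(1 − 0.1097) = 0.151 m/s.
- The two-sided t test of the slope on n − 2 degrees of freedom needs n = 88, with power 0.902 there. The stated sample size is reproduced, which confirms that it is for a continuous linear slope. (If 0.16 is read as the residual SD, n would be 98 and power at 88 would be 0.87.)

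**Step 2: what a correct linear model looks like.** Under these assumptions, simulated linear R² has a median of 0.11 and a 95% range of about 0.02 to 0.26. It is below 0.20 in about 89% of trials. A low R² is the expected result when the plan is right.

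**Step 3: power of the interval model when the relation is linear.** Assume a normally distributed dose cut into k equal-sized groups, of which a share e of the dose variance is kept. Then R²_k = e × 0.1097, the noncentrality is 88 × R²_k / (1 − R²_k), and the F test has k − 1 and 88 − k degrees of freedom.

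| Analysis of dose | e | Power at n = 88 |
|---|---|---|
| Continuous, linear (1 df) | 1 | 0.90 |
| Continuous, 3-knot spline (2 df) | 1 | 0.83 |
| 2 groups, overall test | 0.637 | 0.72 |
| 3 groups, overall test | 0.793 | 0.72 |
| 4 groups, overall test | 0.861 | 0.70 |
| 5 groups, overall test | 0.897 | 0.67 |
| Quartiles, top versus bottom | – | 0.80–0.83 |
| Quartiles, linear trend | – | 0.85 |

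For quartiles: R²_4 = 0.861 × 0.1097 = 0.0945; noncentrality = 88 × 0.0945 / 0.9055 = 9.18; power 0.698. Simulation gives 0.68–0.69, where the linear slope itself simulates at 0.89. The lower top-versus-bottom figure uses only those two groups' data; the higher one pools the residual variance over all four.

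**Step 4: power when the relation is not linear.** Same explained variance and n = 88, by simulation; spline against overall quartile test:

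| True shape | Spline | Quartiles |
|---|---|---|
| Plateau above the median | 0.80 | 0.63 |
| Inverted U | 0.75 | 0.31 |
| Saturating | 0.68 | 0.41 |
| Step at lowest quartile | 0.67 | 0.68 |
| Step at highest quartile | 0.68 | 0.69 |
| Step at median | 0.62 | 0.69 |

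The spline is ahead for each smooth shape tried. Quartiles match it or modestly beat it only for an abrupt step located at a cut point.

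**The case against.** The intervals are a last resort. Continuous dose comes first and nonlinear forms second, and a polynomial would usually catch something like an inverted U before any cutting took place. The figures in Step 3 assume the planned linear relation, which is the case in which the fallback should not be triggered, so they price an unnecessary switch. The article also fixes neither the number of intervals nor the test, and a trend across quartiles loses only about 5 points. All of this stands.

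Two stronger readings are tempting, and the document supports neither. One is that the plan's power simply is about 0.70. That figure needs quartiles, a 3-df overall test, a truly linear relation and a switch actually made; quartiles appear in the article only for other outcomes and for exploratory displays. The other is that an interval model cannot answer the primary objective. The objective is to indicate preliminary efficacy, and the Introduction accepts a comparison of the least with the most compliant participants, which interval means can provide. What the interval model lacks is the direct dose-response estimate, as the protocol says.

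The objection does not show that the fallback is needed. No absolute R-squared threshold is stated, so it is possible rather than certain that a weak but correct linear fit would be rejected; equally, nothing in the text prevents it. The article already allows nonlinear structures, so a continuous alternative is available at the point where the intervals would take over.

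**Conclusion.** The concern holds as a conditional one. The primary analysis contains a fallback that gives up the estimate the study was sized on, and it is entered on an uncriterioned judgement of fit that a correct linear model, with R² of about 0.11, could fail. If that happens, the cost is 18 to 23 points of power for an overall test on two to five equal groups (0.90 to 0.72–0.67), or about 5 to 10 points for a trend or top-versus-bottom test on quartiles (0.85–0.80). These figures rest on the Sample size assumptions, a normally distributed dose, a linear relation and 88 analysed participants. They are not the expected power of the plan as a whole, because the fallback may never be used. The point is worth correcting but does not undermine the design.

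**What to change.** In Primary analysis and Table 3, remove the interval model as a fallback. State that the linear slope of change in gait speed on dose, with its 95% CI, is always reported as the primary estimate. If residual plots show curvature, add a restricted cubic spline with three knots at dose percentiles fixed in advance. Show interval or quartile means as a descriptive figure only, as the article already does for the other secondary outcomes. HOOS ADL then follows automatically, since it copies the primary analysis.

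The cost is a few sentences of wording and no new data. There are two small downsides: a spline is less simple to read than interval means, and its power is slightly lower if the truth is a sharp step at a cut point (0.62 against 0.69 for a step at the median).

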18^. With the PHETHAS-1 trial, we want to use this sensor technology to investigate if a dose-response relationship exists for home-based rehabilitation exercise and recovery after THA, using a prospective cohort study design. By using this technology, we will be able to not only investigate a dose-response relationship on the recovery associated with exercise, but also investigate the preliminary efficacy of home based, rehabilitation exercise after THA. This can be achieved by comparing participants with the least exercise compliance to those with the most. This will indicate whether home-based, rehabilitation exercise “works” better than no or very little rehabilitation exercise, although not a randomized comparison. It will help inform a subsequent large-scale, confirmatory, randomized trial investigating the efficacy of rehabilitation exercise after THA when compared to no or very minimal rehabilitation exercise.

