### Other pre-specified outcomes

Self-efficacy.The general self-efficacy scale
^30^ will be used to measure self-efficacy, defined as an individual's belief in his or her capacity to execute behaviors necessary to produce specific performance attainments. At 3 weeks after surgery.24-hour physical activity (mean upright time/day and mean number of steps/day).An ActivPAL movement-sensor will be used to measure mean time per day in upright position (standing and walking) based on 7 days of data collection. The sensor will be applied 3 weeks after surgery and used the following week. At 4 weeks after surgery.Number of participants with adverse events.Number and type of adverse events will be registered by the physiotherapist 3 and 10 weeks after surgery in the following pre-defined categories: Hip dislocation, infection, fracture, wound seepage, acute myocardial infarction, deep venous thrombosis, readmission and other.Mean change in pain after each exercise session.The visual analogue scale (VAS) will be used to assess pain before and after each exercise session. Data will be summarized as a mean change in pain per exercise session for the entire intervention period. At 10 weeks after surgery.Number of pain flares after exercise sessions.VAS will be used to assess pain before and after each exercise session. Pain flare is defined as an increase in pain of ≥20 mm
^31^. Data will be summarized, both for the first 14 days of the intervention and for the entire intervention period. At 5 and 10 weeks after surgery.Motivation to perform the prescribed exercises.The participants will be asked about their motivation to perform the prescribed exercises. A short questionnaire comprising three questions developed for this purpose will be used (the questionnaire is available as
*Extended data*)
^20^. The possible responses are ordered in 4 levels of motivation on an ordinal scale. At 3 weeks after surgery.Evaluation of the prescribed exercisesThe participants will be asked to evaluate the exercises. A short questionnaire comprising three questions developed for this purpose will be used (the questionnaire is available as
*Extended data*)
^20^. The possible responses are ordered in 4 levels on an ordinal scale. At 10 weeks after surgery.

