### Exploratory analyses

To better understand what may relate to how patients comply with prescribed rehabilitation exercise after THA, we will investigate how different variables relate to exercise compliance (dependent variables: time under tension summary dose and total number of exercise sessions), using uni-variable modelling. Independent variables will be: pain flares (first two weeks of intervention), pain flares (entire intervention period), HOOS pain (baseline), motivation to perform exercises, belief in effect of exercises, self-belief in compliance to exercising, satisfaction with rehabilitation exercise, physical activity (mean upright time/day and mean number of steps/day) and self-efficacy (baseline).

To better understand what may relate to how physically active patients are after a THA, we will investigate how different variables relate to physical activity (dependent variables: mean upright time/day and mean number of steps/day), using univariate modelling. Independent variables will be: pain flares (first two weeks of intervention), HOOS pain (baseline), motivation to perform exercises, self-belief in compliance to exercising, and self-efficacy (baseline).

In the analysis of "result of the operation", the change in score from baseline to follow-up will be presented for each HOOS subscale (pain, symptoms, ADL, QOL) and gait speed. Data will be presented both for each response category of the anchor question, and for the subgroup of patients, who answered "excellent", "very good" or "good" data. This subgroup is considered to be reporting a hip-specific acceptable symptom state. Data will be presented by means with 95% CI or medians and interquartile ranges (IQR). In each response category of the question for "change in hip problems", the change in score from baseline to follow-up will be presented for each HOOS subscale (pain, symptoms, ADL, QOL) and gait speed. Data will be presented by mean scores with 95% CI or median and inter quartile range (IQR).

Furthermore, for each exercise dose quartile, the percentage of patients in each response category of the questions for "result of the operation" and "change in hip problems", will be presented graphically. Finally, HOOS cut points for PASS and MCII will be estimated by the mean score or mean change approach
^40^.

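### The primary dose-response model adjusts for only three candidate confounders of a self-selected dose, may delete each by an undefined criterion, and leaves out baseline variables that the study already collects

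*Protocol article*

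**What the plan says.** The study is a single cohort. Dose is what each participant actually performs at home, and the Intervention section says that nothing beyond normal practice will be done to raise compliance. The Introduction says how preliminary efficacy will be examined: "This can be achieved by comparing participants with the least exercise compliance to those with the most".

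The Primary analysis section names the confounders: "Possible confounding variables (self-efficacy (baseline), physical activity (during intervention), and gait speed (baseline)) will also be included in the models". It then gives the selection rule: "The confounding effect of each variable will be examined by comparison of dose response estimates in models with and without the confounder". And: "If there is no relevant change between the estimates of the models, the confounder will be excluded from the model". What counts as relevant is not defined. Baseline gait speed also falls under a second conditional rule: "If regression to the mean is believed to be present for an outcome, the models of the outcome will additional include the baseline measure".

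Table 3 lists "Age, gender, height, weight, ASA status" for summary statistics only and adds no named confounder. HOOS is measured at 3 weeks (Table 1). The Exploratory analyses section, where "we will investigate how different variables relate to exercise compliance", lists baseline HOOS pain among the candidate predictors. Of physical activity, Other pre-specified outcomes says: "The sensor will be applied 3 weeks after surgery and used the following week".

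**The concern.** Participants who are older, have more comorbidity or have more pain may exercise less and may also recover gait speed at a different rate. Any such variable outside the model puts its own effect into the dose slope. The plan treats baseline pain as a possible determinant of compliance in one section and leaves it out of the primary model in another. The Strength and limitations section explains why activity and self-efficacy are measured, but not why the other variables are left out.

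The deletion rule adds a second weakness. The decision to keep or drop a variable is made after seeing the dose estimate, against a criterion that nobody has written down. If a polynomial or categorical dose model is chosen, which the section allows, there is no single dose estimate to compare.

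The result is meant to help plan and power a randomised trial (Discussion), so a confounded slope would carry forward.

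**Working it through.** **Inputs from the Sample size section.** Target 0.2 m/s over a dose range of 4 hours; SD 1.06 h for dose and 0.16 m/s for change in gait speed; power 0.90; level 0.05 (two-sided assumed); n = 88.

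**Step 1: reproduce the plan's figure.**
- Slope = 0.2/4 = 0.05 m/s per hour.
- Correlation = 0.05 × 1.06/0.16 = 0.331.
- Residual SD = 0.16 × √(1 − 0.331²) = 0.151 m/s.
- A two-sided noncentral t test of the slope needs n = 88, with power 0.903.

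The stated 88 is therefore an unadjusted slope calculation with no allowance for covariates correlated with dose.

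**Step 2: one omitted confounder, no true dose effect.** The documents give no correlations between covariates and dose or outcome, so these are assumed. Let the confounder have the same correlation r with dose and with gait change, after whatever adjustment is made. The SDs are kept at the Sample size values.
- Spurious correlation c = r × r.
- Spurious difference over 4 hours = 4 × c × 0.16/1.06.
- Noncentrality = c × √88/√(1 − c²), t with 86 df, two-sided 5%.

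| r | c | Difference over 4 h (m/s) | Share of 0.2 | False-positive rate |
|---|---|---|---|---|
| 0.2 | 0.04 | 0.024 | 12% | 6.6% |
| 0.3 | 0.09 | 0.054 | 27% | 13.4% |
| 0.4 | 0.16 | 0.097 | 48% | 32.4% |

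**Step 3: the deletion rule alone.** This was simulated with 4000 runs, one measured confounder, both correlations 0.3 and no true effect. The thresholds are assumed because the plan gives none.
- Always adjusting: 5.0% false positives.
- Dropping when the 4-hour difference moves by less than 0.02 m/s: 5.3% (dropped in about 10% of runs).
- Dropping when it moves by less than 0.04 m/s: 6.4% (dropped in about 34%).

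In this scenario, leaving a confounder out of the candidate list costs far more than the deletion step.

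**Step 4: precision with a fixed set.** Power at n = 88 for the planned slope, with six fixed covariates (assumed shares of variance explained):

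| Dose variance explained by covariates | No residual outcome variance explained | 20% of residual outcome variance explained |
|---|---|---|
| 0% | 0.90 | 0.95 |
| 10% | 0.87 | 0.93 |
| 20% | 0.83 | 0.90 |
| 30% | 0.78 | 0.86 |

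Seven covariates instead of six give the same values to two decimals.

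**Step 5: timing of the activity measure.** Activity is recorded in the first of seven exercise weeks, so it follows the start of exposure. Table 2 prescribes one set per exercise in week 1 and two in weeks 2 to 7, so week 1 holds 1/(1 + 6 × 2) = 1/13, about 8%, of prescribed sets.

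**The case against.** The plan already adjusts for baseline gait speed and self-efficacy, if they are retained. Gait speed at 3 weeks plausibly carries part of the influence of age, comorbidity and pain. This stands: the correlations in Step 2 must be those that remain after that adjustment, and at 0.2 the inflation is small. The direction of bias is not known either.

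The authors also state in the Introduction that the comparison is not randomised and is meant to inform a confirmatory trial. That limits the claim, but it does not replace adjustment for data already in hand.

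A reader might infer that adjusting for week-1 activity is plainly an error because it removes part of the exercise effect. The documents do not support that. Most of the dose comes after the activity measurement and cannot have caused it. Adjustment also fits the planned randomised comparison with merely resuming general activity (Discussion). Activity may be a confounder, partly a consequence of early exercise, or both.

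Nor is it a strong point that upright time contains the exercise itself. Table 2 implies 5 s × 15 repetitions = 75 s per set. Seven sets (three band exercises on two legs, plus sit-to-stand) take 8.75 minutes, and four sessions a week average about 5 minutes per day, against an outcome in hours per day.

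Finally, a reader might take the deletion rule to be a large source of false positives in itself. Step 3 does not show that.

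**Conclusion.** The point holds in a limited form. The primary model has a closed list of three candidates for a self-selected dose, any of which can be deleted on an undefined criterion, while plausible baseline confounders are collected and left out without a stated reason. This is a fixed choice and not a detail left to another document, since the Abstract says that the paper includes the statistical analysis plan.

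The illustrated size is a spurious 0.024 to 0.097 m/s against a target of 0.2, and a false-positive rate of 6.6% to 32.4%. These are scenarios resting on assumed residual correlations of 0.2 to 0.4 and a single confounder. They should not be read as this study's actual error rate or as evidence that its slope will be biased upward. The omission is the main weakness; the deletion rule matters chiefly because it leaves the final model open to judgement after the estimate is seen.

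**What to change.** - Pre-specify one primary adjustment set with no deletion step: baseline gait speed, self-efficacy, age, sex, BMI (from height and weight), ASA status and HOOS pain at 3 weeks. Baseline gait speed then no longer depends on either conditional rule.
- Report the dose estimate both with and without week-1 physical activity, and say why: it is measured after exercise starts and its role is not settled.
- Word the conclusion as an adjusted association between dose and change in gait speed, not as efficacy.

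Excluding participants whose adverse events limited their exercise is not advised. The plan registers the number and type of events, not whether exercise was limited, and such an exclusion would condition on something that happens after baseline.

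**Cost.** No new data, a few degrees of freedom and one additional reported estimate. Precision may fall: power at n = 88 would be about 0.87 to 0.78 if the covariates explain 10% to 30% of dose variance and none of the outcome, and 0.93 to 0.86 if they also explain 20% of residual outcome variance.
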